## Methods/Design

In this proof-of-principle study, a total of 60 adult participants diagnosed with ADHD (combined, hyperactive, or inattentive type) are randomly blockwise assigned to SCP, NIRS, or electromyogram (EMG) feedback groups (n = 20 each) stratified for age, sex, and educational level. This is the first study to investigate and compare the efficacy of these treatment modalities in an adult ADHD population.

Twenty healthy controls matched for age, sex, IQ, and pre- and post-treatment duration will be included in the neurophysiological assessments for pre- and post-treatment measurement in order to establish “expected” activation patterns and allow for a more thorough interpretation of changes following the neurofeedback treatment. The study objectives are as follows:Assess whether there are physiological differences (EEG and ERP) in ADHD participants compared to healthy controls.Assess whether adult participants are able to demonstrate learning of cortical self-regulation.Assess whether treatment leads to an improvement in cognition (that is, attention and working memory) and behavior (that is, restlessness and impulsivity), and changes in specific EEG or NIRS parameters.Assess whether specific methods and protocols are more efficacious in changing behavioral, cognitive, and EEG and NIRS outcome variables.Assess whether changes are stable at the 6-month follow-up.Assess whether specific methods and protocols differ in the stability of cortical self-regulation and clinical effects at the 6-month follow-up.Assess whether the efficiency of the different training protocols differs depending on individual neurocognitive baseline parameters (for example, frontal lobe activation during neuropsychological assessments; baseline CNV etc.).

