### Study flow

At baseline/pre-treatment, participants are screened and diagnosed with ADHD, assessed with a battery of neuropsychological questionnaires for evaluation of cognitive and behavioral outcome variables, and evaluated using a 22-channel NeXus-32 (Mind Media B.V. with Biotrace^+^ Software, Herten, The Netherlands) continuous EEG recording (eyes closed, eyes open, auditory oddball, and auditory Go/NoGo task). Moreover, concentration changes of O_2_Hb and HHb during three executive functioning tasks (working memory, Go/NoGo, and word fluency) are measured by a 52-channel continuous wave NIRS-system (ETG-4000, Hitachi Medical Co., Tokyo, Japan). At mid-treatment (that is, after 15 sessions), post-treatment (after 30 sessions), and 6-month follow-up, the neuropsychological assessments are repeated.

Healthy controls (n = 20) undergo the EEG/NIRS assessment for the pre- and post-treatment measurement points. See Figure 1 for an illustrated overview of the study flow.

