##### Culture Fair Test-20 Revised (CFT-20-R; screening and follow-up)

The CFT-20-R is a nonverbal intelligence test [62]. This test is used to determine inclusion and treatment effects over time.

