##### Test d2- Revision Aufmerksamkeits- und Konzentrationsstest (d2-R; screening and evaluation of outcome)

The d2-R is a 10-minute assessment in which participants cross out the target letter from a series of similar letters [67]. The total number of items processed minus errors indicates combined speed and accuracy scores for attentional and inhibitory control. This test is used to assess attention in comparison with healthy controls and for treatment effects over time.

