### Primary and secondary endpoints

As a primary outcome, the changes in core symptoms will be assessed by the ADHS-SB (self-report) and the FEA-AFB as well as WRI (third party evaluation). Variables of secondary outcome will include cognitive factors (that is, attention, intelligence, response inhibition, and working memory) and changes in specific EEG/ERP and NIRS parameters (that is, relative and absolute power and frequency ratios, concentration changes in O_2_Hb and HHb), as well as achievement of self-regulation.

For the pre- and postevaluation, the independent variable is the treatment (SCP, NIRS, or placebo feedback). In addition, for the comparison of the neurophysiological and cognitive data the health status (healthy and ADHD participants) constitutes another independent variable.

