### Statistical analysis

#### Electroencephalogram, near-infrared spectroscopy, electromyogram and behavioral data

All dependent variables will be tested for effects within and between groups by an analysis of variance (ANOVA) (three groups x four assessment points). For the comparison of pretest-data between ADHD and healthy subjects, t-tests and/or one-way ANOVAs will be applied. If normal distribution cannot be assumed, non-parametric tests will be used.

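### The single 3 x 4 ANOVA for all dependent variables does not match Table 1 for the WRI (a primary measure), the d2-R and the CFT-20-R

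*Protocol article*

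**What the plan says.** The Statistical analysis section of the Protocol article applies one ANOVA layout to every dependent variable, for effects both within and between groups: "three groups x four assessment points". The only alternative it gives for these comparisons over time is non-parametric testing if normality cannot be assumed. The t-tests and one-way ANOVAs it also mentions are for the pretest comparison with healthy subjects.

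The outcomes come from Primary and secondary endpoints. For the primary outcome, "the changes in core symptoms will be assessed by the ADHS-SB (self-report) and the FEA-AFB as well as WRI (third party evaluation"). For the secondary outcomes, "Variables of secondary outcome will include cognitive factors (that is, attention, intelligence, response inhibition, and working memory").

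The instrument descriptions confirm that the three tests at issue are outcomes and not only screening tools. For the d2-R: "This test is used to assess attention in comparison with healthy controls and for treatment effects over time". The WRI and CFT-20-R entries also give treatment effects as a purpose.

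Three other places bear on the schedule:
- Study flow: "At mid-treatment (that is, after 15 sessions), post-treatment (after 30 sessions), and 6-month follow-up, the neuropsychological assessments are repeated".
- The heading of the intelligence test: "Culture Fair Test-20 Revised (CFT-20-R; screening and follow-up").
- One of the study objectives: "Assess whether changes are stable at the 6-month follow-up".

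**The concern.** A group-by-time ANOVA with four time levels needs a scheduled score at each of the four levels. If an instrument is never given at one of them, that cell is empty by design and the model has to be changed before it can be run. The analysis sentence makes no exception, so for some outcomes the article prescribes a layout that its own schedule rules out.

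Two things are at stake. First, the WRI is a primary measure, and which of its time levels enter the test is not fixed by the text. In a trial where the Randomization and blinding section says that neither participants nor assessors are blinded, that choice should not be left until the data are in hand. Second, the trial is ongoing. If it is the schedule that is wrong and not the analysis sentence, visits run according to Table 1 will not collect the missing scores, and these cannot be recovered later.

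**Working it through.** **Inputs.** Three groups of 20, so N = 60 (Methods/Design). Four time levels (Statistical analysis). Marked visits per instrument (Table 1), with the screening or pre-test mark taken as baseline.

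**Degrees of freedom.** For g groups and k time levels with complete cases and no sphericity correction:
- group-by-time df = (g − 1)(k − 1) = 2(k − 1)
- error df = (N − g)(k − 1) = 57(k − 1)

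**Plan's own figure first.** With k = 4 the stated layout gives 2 × 3 = 6 and 57 × 3 = 171. Table 1 reproduces k = 4 for four of the seven entries checked:

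| Instrument | Role | Visits marked in Table 1 | k | Layout supported | df |
|---|---|---|---|---|---|
| ADHS-SB | primary | screening, in-between, post, follow-up | 4 | 3 x 4 | 6; 171 |
| FEA-AFB | primary | screening, in-between, post, follow-up | 4 | 3 x 4 | 6; 171 |
| WRI | primary | screening, post, follow-up | 3 | 3 x 3 | 4; 114 |
| d2-R | secondary | screening, post | 2 | 3 x 2 | 2; 57 |
| CFT-20-R | secondary | screening, post | 2 | 3 x 2 | 2; 57 |
| EEG | secondary | pre-test, in-between, post, follow-up | 4 | 3 x 4 | 6; 171 |
| NIRS | secondary | pre-test, in-between, post, follow-up | 4 | 3 x 4 | 6; 171 |

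The marks for the four-visit instruments fall in the expected columns, so the shorter rows are not a result of how the table was read. The WRI lacks the mid-treatment level. The d2-R and CFT-20-R lack mid-treatment and follow-up.

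**CFT-20-R heading against Table 1.** The heading names follow-up as the second occasion. Table 1 marks post-test and leaves the follow-up test blank. One of the two is wrong, or the heading uses follow-up loosely.

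**Study flow against Table 1.** The sentence on repeated neuropsychological assessments can be read in two ways:
- Narrow: in the last study objective and in Neurophysiological predictors, the same term refers to the sessions in which EEG and NIRS activity is recorded. On that reading it agrees with Table 1, where both have four marks.
- Broad: the same Study flow section also describes a baseline questionnaire battery for cognitive and behavioural outcomes. On that reading the d2-R and CFT-20-R would have four points and Table 1 would be wrong. The WRI, a structured interview, is less clearly covered.

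**Six-month data on cognition.** Table 1 has no d2-R at follow-up, but it does mark EEG and NIRS there. The EEG session includes the three-tone oddball and the auditory Go/NoGo task, both yielding reaction time, its variability and error rates. The NIRS session includes the n-back working memory task.

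**Sample size.** The stated n = 20 per group is unaffected. A two-sample t calculation with effect size 0.81, one-sided α = 0.05 and 80% power gives 19.56, rounded up to 20 (power 0.808). It uses no time levels.

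**The case against.** The strongest reply is that this is only loose wording. The planned method is a group-by-time ANOVA, and anyone running it would use the visits that exist: 3 x 3 for the WRI, 3 x 2 for the other two. Time levels per instrument are detail that a condensed article may leave to a full protocol or analysis plan, neither of which is shown.

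Most of this stands, and it limits the point. A reader might infer that the WRI has no executable analysis, or that every participant counts as incomplete on it. The documents do not support either: the absent levels were never scheduled, so no planned score is lost and the sample is not reduced.

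A reader might also infer that 6-month stability of attention cannot be assessed. The objective names no instrument, and the EEG-task measures are collected at follow-up. Only the d2-R and CFT-20-R lack a 6-month value in Table 1. Nor does Study flow clearly contradict the table, because the narrow reading is available.

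What does not stand is the appeal to omitted detail. The article did not leave the layout open. It stated one, applied it to all dependent variables, and its own table rules that layout out for a primary measure.

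**Conclusion.** The point holds as a mismatch between the analysis sentence and the schedule. It affects one of three primary measures (WRI) and two secondary tests (d2-R, CFT-20-R). Two of three primary measures and the EEG and NIRS outcomes fit the stated model.

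This rests on Table 1 being the schedule in force. If the broad reading of Study flow were the true schedule, the d2-R and CFT-20-R would fit 3 x 4 and Table 1 would need the correction instead. Either way two places in the article disagree and have to be reconciled.

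Severity is should-fix. It might seem to follow that the primary analysis should be replaced for all instruments by a comparison at post-test, the one post-baseline visit they share. The mismatch gives no ground for that, because naming the time levels repairs it fully.

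**What to change.** 1. In Statistical analysis, state the time levels per instrument. On the Table 1 schedule these are 3 x 4 for ADHS-SB, FEA-AFB, EEG and NIRS, 3 x 3 for the WRI, and 3 x 2 for the d2-R and CFT-20-R. For the last two, comparing post-test scores adjusted for the baseline already collected answers the same question, usually with better precision.
2. Make the CFT-20-R heading and Table 1 agree on the second testing occasion.
3. In Study flow, say which assessments are repeated at each visit.
4. State that 6-month stability of attention rests on the EEG-task measures. Alternatively, and optionally, add the 10-minute d2-R to the existing follow-up visit.

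Items 1 to 3 and the first option in item 4 cost only wording and should be settled before analysis. Adding the d2-R is a schedule change in an ongoing trial, and it cannot recover follow-up visits already completed.

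### The switch to non-parametric tests when normality fails lets the data choose the test and could leave the group-by-time question untested

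*Protocol article*

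**What the plan says.** Protocol article, Statistical analysis, first subsection (EEG, NIRS, EMG and behavioral data):

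- Scope: "All dependent variables will be tested for effects within and between groups".
- Method: an ANOVA with "three groups x four assessment points".
- Patients against healthy controls at baseline: "For the comparison of pretest-data between ADHD and healthy subjects, t-tests and/or one-way ANOVAs will be applied".
- Fallback, in the last sentence: "If normal distribution cannot be assumed, non-parametric tests will be used".

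Two other sections set the question that these tests must answer. The objectives under Methods/Design include: "Assess whether specific methods and protocols are more efficacious in changing behavioral, cognitive, and EEG and NIRS outcome variables". Primary and secondary endpoints defines the primary outcome as a change: "the changes in core symptoms will be assessed by the ADHS-SB (self-report) and the FEA-AFB as well as WRI". Both call for a comparison of change between arms. In a group by time ANOVA, that comparison is the interaction.

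**The concern.** The rule makes the choice of test depend on the observed distribution, outcome by outcome. Because the analysis covers all dependent variables, the rule reaches the three primary scales.

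The rank tests that most analysts would substitute come as separate pieces: Kruskal-Wallis between groups, and Friedman or Wilcoxon within a group. The stated aim of testing effects within and between groups fits those pieces well. None of them contains a group-by-time term. If ADHS-SB passed the check and FEA-AFB failed it, the first could be judged on differential change and the second on separate within-arm improvements.

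That matters in this design. The EMG arm is there to separate specific from nonspecific effects, so improvement in all arms is expected. Within-arm significance cannot tell the two kinds of effect apart.

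**Working it through.** **Inputs from the article.** Three groups with 20 in each (Methods/Design). Four assessment points (Statistical analysis). Effect 0.81 SD, alpha 0.05, one-sided, power at least 80% (Sample-size calculation). In Table 1, ADHS-SB and FEA-AFB are listed at four occasions, WRI at three (screening, post-test, follow-up), and d2-R and CFT-20-R at two.

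**Inputs assumed.** Normal data; equal correlation between occasions within a person; 5% two-sided or omnibus tests. The article gives no correlation, so a range is shown where it matters.

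**The plan's own figure.** A one-sided two-sample t-test with d = 0.81 and alpha 0.05 needs 20 per group (exact power 80.8%). The stated 20 reproduces and is not in dispute. The article gives no figure for the switch.

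**Step 1: can separate rank tests mislead about differential change?** Simulation, 3,000 runs, 20 per arm, correlation 0.6, the same improvement in all three arms (means 0, -0.3, -0.5, -0.5 SD), so there is no group-by-time effect:

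- Friedman test pooled over arms: rejects in 96% of runs.
- Friedman test in each arm: significant in at least one neurofeedback arm but not in EMG in 37% of runs.
- Kruskal-Wallis on pre-to-post change: rejects in 5.7%, close to the nominal 5%.

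The first two are valid tests of time within groups. They do not test whether change differs between arms. The third does.

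**Step 2: how often might the switch be triggered by chance?** This is an illustration, because the article states no such check. Suppose a 5% normality test is made in every cell and any rejection triggers the switch. With independent cells, the probability is 1 - 0.95^k:

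| Occasions | Cells k | Chance switch |
|---|---|---|
| 4 | 12 | 1 - 0.95^12 = 46.0% |
| 3 (as WRI) | 9 | 1 - 0.95^9 = 37.0% |
| 2 | 6 | 1 - 0.95^6 = 26.5% |

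Simulated Shapiro-Wilk tests with 20 per cell and 12 cells, on exactly normal data, give 45.1% at correlation 0.3, 44.6% at 0.5, 43.0% at 0.7, 41.0% at 0.8 and 36.6% at 0.9. With a 1% test level the independent-cell figure is 1 - 0.99^12 = 11.4%.

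**Step 3: what does ranking cost in power?** Suppose both active arms improve by 0.81 SD and EMG does not. The between-arm sum of squares in SD units is 20 x 0.81^2 x 2/3 = 8.748. The noncentrality is this figure divided by the residual variance. At an assumed baseline-post correlation of 0.6:

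| Analysis | Residual variance | Noncentrality | Power |
|---|---|---|---|
| ANOVA on post scores | 1 | 8.748 | 73% |
| ANOVA on change | 2(1 - 0.6) = 0.8 | 10.935 | 83% |
| Baseline-adjusted (ANCOVA) | 1 - 0.6^2 = 0.64 | 13.669 | 90-91% |

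By simulation, Kruskal-Wallis has about 70-71% power on post scores and about 81% on change scores. Like for like, ranking costs about 73 - 71 = 2 to 3 points on post scores and 83 - 81 = 2 points on change. A rank version of the ANCOVA had 86.9% against 90.6%, nearly 4 points. Most of the distance from 70% to 90% comes from the use of baseline.

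**The case against.** The strongest reply has four parts.

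1. *The article does not say how normality is judged.* Its wording also fits a graphical check, a residual check or a judgement about the type of variable. This stands. The figures in step 2 describe an assumed procedure, and a reader should not infer that nearly half of the outcomes will be switched.
2. *Rank methods can address differential change.* Kruskal-Wallis on change scores does so directly, as step 1 shows, and rank-based factorial methods exist. The article excludes neither. This also stands: the interaction could be lost, but it is not certain to be.
3. *The rank route hardly loses power.* This stands for like-for-like comparisons. It would be wrong to read the gap of about 20 points between Kruskal-Wallis on post scores and ANCOVA as the price of the switch. ANCOVA is not the planned analysis, and the gap comes mainly from ignoring baseline. The calculations also use normal data, whereas the fallback is meant for other data.
4. *The choice of rank test and the normality criterion belong in an analysis plan that is not shown.* Their absence is indeed no finding. But naming them later would not cure a rule, stated here, under which the data pick the test. Nor does anything in the article require the fallback to keep the comparison of change between arms.

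**Conclusion.** The point holds in a limited form. The stated rule lets the data select the test for all dependent variables, the primary scales included, and it does not protect the group-by-time question set by the objectives and by the definition of the primary outcome. Some outcomes could therefore be left without a test of differential change, and the three primary scales could be analysed by methods that answer different questions.

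The patient versus healthy-control comparison at pretest is unaffected. It has no interaction, and a rank-sum or Kruskal-Wallis test is a direct substitute there.

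On size, the chance-switch figures hold only under a per-cell 5% check that the plan does not state. The direct power cost of ranking is small. The larger practical gain lies in baseline adjustment: about 90% power against 83% for ANOVA on change, at an assumed correlation of 0.6 and an effect of 0.81 SD in both active arms. This is a weakness of the analysis rule that should be corrected. It does not show that the planned comparison will fail.

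**What to change.** For the between-arm comparisons of continuous outcomes:

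- Delete the switch that depends on normality.
- Fix in advance one baseline-adjusted linear model (a mixed model where all occasions are used), with the between-arm contrast of change as the deciding test.
- Check residuals graphically, without letting the check change the deciding test.
- Report a permutation, bootstrap or rank analysis of the same contrast as a named sensitivity analysis.

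The fallback may stay for the pretest comparison with healthy controls. The cost is a few sentences of analysis wording and a little programming. Recruitment, treatment and assessments do not change.

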#### Neurophysiological predictors

To investigate neurophysiological predictors of treatment outcome, target parameters of the baseline NIRS, EEG, and peripheral physiology data assessments will be analyzed in all treatment groups (SCP, NIRS, and EMG). Specific to the NIRS assessment parameters, mean task-related activation (changes in the concentration of O_2_Hb and HHb) during the baseline assessment will be individually calculated for both the 2-back condition of the working memory (n-back) task and the NoGo condition of the Go-NoGo paradigm. Specific to the EEG assessment parameters, like mean relative theta and relative beta power and theta/beta ratios will be calculated for frontal and central ROIs during eyes open and eyes closed resting state conditions. Additionally, P300 and CNV amplitudes and latencies for these ROIs will be calculated during neuropsychological assessments. The peripheral data from heart rate, respiration, and SCL will be used to assess the peripheral arousal during active (ERP tasks) and resting (eyes open/eyes closed) conditions. These parameters will then be used as independent variables in a regression analysis to predict treatment success (as indicated by changes in psychometric scores in the ADHD symptom scales).

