Additionally, neurophysiological predictors of treatment outcome will be investigated. Target parameters of the baseline NIRS and EEG assessments will be used as predictors in regression analyses. Based on previous findings regarding the prediction of treatment outcome via EEG markers of frontal lobe function in schizophrenic patients [50], we expect treatment effects to be particularly pronounced in participants with weak activation in the baseline frontal lobe assessments, especially for the NIRS feedback arm that is specifically focused on strengthening frontal lobe function. Regarding the EEG baseline data, mean relative theta and relative beta power as well as theta/beta ratios will be calculated for frontal and central regions of interest (ROI) during the eyes open and eyes closed resting state conditions. Additionally, P300 and CNV amplitudes and latencies will be calculated during neuropsychological assessment. Research indicates that adult ADHD participants possess elevated theta/beta ratios [13,14], which have been found to discriminate ADHD participants from healthy control populations [51,52]. These ratios may have prognostic value for prediction of outcome after stimulant medication as well as after neurofeedback treatment [18]. Elevated theta/beta ratios are hypothesized to reflect task-related brain “activation” and serve as a discriminant of behavioral performance [53]. Dominant slow wave activity has been linked with reduced auditory oddball P300 activity [54] and stimulant medication response [52], while larger pre-training CNV activation has been linked with larger symptom reductions following SCP feedback [55]. Therefore, we expect effects to be particularly pronounced in participants with elevated theta/beta ratios and decreased P300 amplitude but greater CNV negativity at baseline assessment.

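### About 30 baseline parameters (27 to 34) are named as regression predictors for at most 60 patients, with the theta/beta ratio listed beside both its components, so the predictor results would be unreliable

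*Protocol article*

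**What the plan says.** The protocol article, Neurophysiological predictors, says that baseline NIRS, EEG and peripheral parameters "will be analyzed in all treatment groups (SCP, NIRS, and EMG"). It then lists them:

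- NIRS: "mean task-related activation (changes in the concentration of O_2_Hb and HHb"), "for both the 2-back condition of the working memory (n-back) task and the NoGo condition of the Go-NoGo paradigm".
- Resting EEG: "mean relative theta and relative beta power and theta/beta ratios will be calculated for frontal and central ROIs during eyes open and eyes closed".
- ERP: amplitude and latency of P300 and of CNV in the same two regions.
- Peripheral: heart rate, respiration and skin conductance, during the ERP tasks and at rest.

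The list ends with the rule "These parameters will then be used as independent variables in a regression analysis", the outcome being change on the ADHD symptom scales. The section names no selection, reduction, shrinkage or validation step.

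Methods/Design gives the sample: "a total of 60 adult participants diagnosed with ADHD", in "feedback groups (n = 20 each").

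The Background has directional hypotheses for far fewer markers. It expects larger effects with weak baseline frontal activation, and also says "we expect effects to be particularly pronounced in participants with elevated theta/beta ratios and decreased P300 amplitude but greater CNV negativity".

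**The concern.** The number of named predictors is about half the number of patients and exceeds the number in any one arm. A least-squares model of that size fits noise closely. Its raw R-squared would look impressive with nothing behind it, and some coefficients would be nominally significant by chance.

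The EEG list adds a second problem. It places the theta/beta ratio beside relative theta and relative beta for the same regions and eye states. The ratio is a hypothesised marker, but in a joint model its coefficient describes the ratio at fixed values of its own numerator and denominator. That is not the hypothesis in the Background.

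At stake is the last of the seven objectives in Methods/Design, which asks whether the efficiency of the protocols depends on baseline neurocognitive parameters. Predictors reported from such an analysis would be unlikely to replicate.

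**Working it through.** **The plan's own figure.** Sample-size calculation states 20 per group for an effect size of 0.81, one-sided alpha 0.05 and power of at least 80%. A one-sided two-sample t-test needs 19.56 per group, rounded up to 20, with power 80.8%. The figure reproduces, but it sizes a two-group comparison and not a regression.

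**Counting the predictors** (from Neurophysiological predictors)

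| Block | Count |
|---|---|
| NIRS: 2 haemoglobin signals × 2 tasks | 4 |
| Resting EEG: 3 measures × 2 regions × 2 eye states | 12 |
| P300: amplitude and latency × 2 regions | 4 |
| CNV: amplitude and latency × 2 regions | 4 |
| Peripheral: 3 signals × active and resting | 6 |
| **Total** | **30** |

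- Lower reading: one summary per peripheral signal, 4 + 12 + 4 + 4 + 3 = 27.
- Higher reading: P300 taken from both oddball tasks in the Assessments, 4 + 12 + 8 + 4 + 6 = 34.

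**Reading A: all predictors in one unpenalised model.** With p predictors, n patients and no true effect, expected raw R-squared = p/(n − 1). With n = 60:

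- p = 27: 27/59 = 0.46
- p = 30: 30/59 = 0.51 (95% range 0.33 to 0.68; 60 − 1 − 30 = 29 residual degrees of freedom)
- p = 34: 34/59 = 0.58

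A null simulation with independent predictors (4,000 runs each) gave mean R-squared 0.46, 0.51 and 0.58. At least one coefficient had p < 0.05 in 62%, 64% and 66% of runs. These rates are per symptom scale.

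The article gives no dropout rate. With an assumed 10% or 20% (n = 54 or 48), 30 predictors give 30/53 = 0.57 or 30/47 = 0.64.

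**Within one arm.** With n = 20 there are 19 degrees of freedom after the intercept. Any count from 27 to 34 exceeds this, so least squares has no unique solution and fits the data exactly.

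**Reading B: one predictor per model.** Primary and secondary endpoints names three symptom measures (ADHS-SB, FEA-AFB, WRI).

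- 30 × 3 = 90 tests; 90 × 0.05 = 4.5 expected false positives.
- Over the range 27 to 34: 81 to 102 tests, 4.1 to 5.1 expected.

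**Ratio with its components.** The article gives no spread for theta or beta, so this part is an assumption. With independent lognormal theta and beta, the variance inflation factor of the ratio is about 31 at a coefficient of variation of 15%, 6 at 35% and 3.7 at 50%.

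**Four-marker model.** Expected null R-squared is 4/59 = 0.07.

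**The case against.** The strongest reply is that the article does not fix a single full model. The abstract and the Background speak of regressions in the plural, and model building is commonly left to an analysis plan, which is not shown. This stands in part. A reader might infer that the trial's regression will explain half the variance by chance; the document does not support that as a flat statement, because it holds only if every parameter enters one unpenalised model. It does not remove the problem. The section assigns all the listed parameters as independent variables, and separate models exchange overfitting for multiplicity.

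Other points that stand:

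- **The count is not a strict floor.** The article gives no total, and the peripheral block can be read as three or six variables. The Auditory Go/NoGo task section plans CNV amplitude only; dropping CNV latency in two regions from the lower reading leaves 25, and 25/59 = 0.42. The EEG list is also worded as illustrative, which could raise the count.
- **Only raw R-squared is inflated.** Under the null, expected adjusted R-squared is zero and the overall F-test keeps its 5% level. The article does not say which criterion will be reported.
- **The variance inflation figure depends on an assumed spread.** Collinearity of this kind does not in itself bias predictions; it harms the reading of the ratio's coefficient.
- **Separate models per arm are not stated.** A pooled model fits the wording equally well.
- **Prediction is not a main aim**, although its place in the abstract might suggest so. It comes last of seven objectives, is neither a primary nor a secondary endpoint, and the trial is described as proof of principle.

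**Conclusion.** The concern holds in conditional form. The article names roughly 27 to 34 predictors for at most 60 patients. In one unpenalised model, the expected raw R-squared with no true predictor is 0.46 to 0.58, and about 65% of trials would show at least one nominally significant coefficient per scale. A model within one arm could not be fitted uniquely. As single-predictor tests, 30 predictors on three scales give 4 to 5 expected false positives.

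This is a fault in a stated analysis rather than a missing detail: following the text gives unreliable predictors on either reading. It affects a secondary objective only. The comparison of the three groups on the primary outcomes does not depend on it.

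The figures assume complete data on 60 patients, no true effects, tests at 0.05 without correction and, for the simulated rates, independent predictors.

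**What to change.** 1. Limit the hypothesis-testing predictor model to the four markers with hypotheses in the Background: prefrontal activation, theta/beta ratio, P300 amplitude and CNV amplitude.
2. For each marker, fix one measure (signal, task, region and eye state, as applicable) before outcome data are examined.
3. Do not enter relative theta and relative beta in the same model as their ratio.
4. Label all other parameters exploratory, analyse them with a penalised model, and report cross-validated R-squared instead of the in-sample value.

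The 0.07 for four markers is for main effects only. If the objective about differences between protocols is tested in the same model, two arm terms and eight arm-by-marker terms bring it to 14 terms, and 14/59 = 0.24. That is a further reason to keep the marker list short.

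The cost is a change of wording in the protocol or analysis plan and a little more analysis work. No new data are needed. The downside is that fewer parameters can be claimed as predictors.
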